## Abstract

**Aim:**

There are limited studies in Tanzania concerning the modality of preparing patient navigators and the influence of patient navigation strategies on cervical cancer screening. This protocol describes the preparation of patient navigators and assesses the impact of a patient navigation strategy on promoting cervical cancer screening uptake, knowledge, awareness, intention, and health beliefs.

**Design:**

This is a protocol for a community-based randomized controlled trial.

**Methods:**

The method is categorized into two phases. (1) Preparing patient navigators, which will involve the training of five patient navigators guided by a validated training manual. The training will be conducted over three consecutive days, covering the basic concepts of cervical cancer screening and guiding navigators on how to implement a patient navigation strategy in the communities. (2) Delivering a patient navigation intervention to community women (COMW) which will involve health education, screening appointments, navigation services, and counseling. The study will recruit 202 COMW who will be randomized 1:1 by computer-based blocks to either the patient navigation intervention group or the control group.

**Public contribution:**

The study will prove that the trained patient navigators are easily accessible and offer timely and culturally acceptable services to promote cervical cancer screening uptake in communities.

## Introduction

Globally, cervical cancer is the fourth most common cancer (1), and a leading cause of death (2). An estimated 569,847 new cervical cancer cases and 311,365 deaths worldwide occur annually (3). The rate of new cervical cancer cases is 7.5 per 100,000 women per year, and the death rate is 2.2 per 100,000 women per year (4). Cervical cancer can often be prevented by having regular screenings to find any precancerous conditions and treat them (5). Even though the World Health Organization (WHO) has adopted a global strategy for eliminating cervical cancer by ensuring that 70% of the population is screened and 90% of those diagnosed with cervical cancer disease are treated (6), the screening status remains unsatisfactory in developing countries (7).

## Cervical cancer in Tanzania

The incidence rate of cervical cancer in Tanzania is 54 per 100,000 (8–10), which is the fifth highest in the world (11). Despite the fact that cervical cancer screening (CCS) services in Tanzania are free of cost (12, 13), only 6%–21% of women participate in CCS (14). A knowledge deficit about the disease and screening remains a predominant factor for poor participation in CCS (15). Public health education is a recommended approach to improve the proportion of screening uptake (16).

Harold P. Freeman initiated patient navigation in the 1990s to eliminate barriers to a timely diagnosis of breast cancer and treatment and reduce cost, whereby the result was a drop in late-stage diagnosis from 50% to 20% and an increase in survival from 39% to 70% (17). The patient navigation approach has been widely applied to promote CCS behavior in women (9). In many studies, patient navigators are referred to as community health workers (CHWs) (18–22). Patient navigators have successfully influenced many women to utilize CCS services (18, 19, 20–27, 28, 29), with increased participation of women in screening ranging from 56% to 89% (19, 20, 23, 24, 27, 28). This is because CHWs not only deliver education but also help women overcome screening barriers (18, 30, 31). Women who receive education from patient navigators have an increased knowledge and positive perception of CCS (19, 22). Education delivered by patient navigators is provided in a culturally accepted manner as they live in the same community as the women who receive the teaching (32), and follow-ups conducted by patient navigators for the women who receive the education are very effective (9, 33). Even though patient navigation is an important approach to increasing CCS uptake, there is a lack of studies in Tanzania concerning how to prepare patient navigators and the effect of a patient navigation strategy in promoting screening uptake. Therefore, the proposed study aims to assess a systematic approach to preparing patient navigators and assess the impact of patient navigation on promoting screening uptake, knowledge, awareness, health beliefs, and intention.

## Methods

Since the study involves the preparation of patient navigators and the implementation of patient navigation for community women (COMW), separate detailed methodologies are described below.

### Preparation of the patient navigators

#### Recruitment of potential patient navigators

Patient navigators are defined as the health workforce conducting outreach beyond healthcare facilities or who are based at peripheral health posts that are not staffed by doctors or nurses, who are either paid or volunteers, who are not licensed, and who have fewer than 2 years of training but at least some training, if only a few hours (34). The roles of patient navigators involve community mobilization, health promotion, provision of preventive services, provision of clinical services, epidemographic surveillance, and record-keeping (35). Therefore, non-healthcare professionals who are considered to be potential patient navigators will be recruited into the study through purposive sampling. The recruitment process will involve local community leaders who will propose the potential participants. Participants will be recruited if they are women, residents of the study area (21, 29, 36, 37), have community influence, are well respected in their communities, and have a secondary/high school/university level of education (19, 36). All the suggested participants will be visited by healthcare professionals at their homes to ask about their interests and willingness and further check whether they are eligible. Ten eligible patient navigators will be asked to give their informed consent (19, 24, 26, 29), administered a baseline questionnaire, and invited to participate in the training sessions.

#### Training patient navigators

The training of five patient navigators will be facilitated by a nurse with a master's degree in oncology nursing who is currently working in the cervical cancer screening department. The training will be conducted using a training manual that is already developed by the principal investigator. The development of the manual has undergone five steps: (i) development of the first draft of the training manual through a systematic review study (38), (ii) revision of the training manual based on the available content in the World Health Organization facilitator guide (39), (iii) revision of the training manual based on a cross-sectional study (40), (iv) revision of the training manual based on an expert's comments, and (v) translation of the training manual from English into Swahili. The theory of planned behavior (TPB) and the health belief model (HBM) were used during the development process.

Patient navigators will receive training on three consecutive days (19, 21, 25, 26, 29, 41) from 9:00 a.m. until the scheduled activities for the day are accomplished (41). A healthcare professional will facilitate the training in Swahili (19, 24, 26, 29). Even after the 3-day training, the healthcare professional will continue to provide ongoing education to enable the patient navigators to acquire more knowledge and skills (21, 24, 29). In the 3-day training, seven sessions will be conducted. The training will begin with a 1-h open session; the patient navigators will be registered and welcomed to the training, followed by a self-introduction from the healthcare professional and the patient navigators. The healthcare professional will clearly state the goal, objectives, and rules of the training. Interactive learning visual aids, discussions, and role-playing will be used throughout the sessions. A PowerPoint (PPT) and projector will be used during the training. The healthcare professionals should prepare marker pens, notebooks, whiteboards, blackboards, and all other required teaching materials. There will be breaks between sessions with free lunches and drinks.

Table 1 shows details about the content to be delivered on specific days and in specific sessions, as explored in different studies (18, 23, 25, 26, 29). The first day will have two sessions with 1 h for each session. Session 1 will cover the roles of patient navigators while in session 2, patient navigators will learn about female reproductive organs. The second day will have a total of two sessions, whereby session 3 will last for 4 h to cover an introduction to cervical cancer, including the cause, risk factors, signs, and symptoms of cervical cancer. Session 4 is scheduled for 2 h and will cover preventive measures for cervical cancer. Furthermore, the third day will have three sessions, of which session 5 will last for 1.5 h and the patient navigators will learn how to deliver health education and encourage women to complete screening. Session 6 is scheduled for 2 h, teaching patient navigators about home visits, especially the importance of home visits, and how to talk to a woman who misses her scheduled appointment date. Session 7 will last for 2 h, teaching the patient navigators about healthcare facilities with cervical cancer screening services.

**Table 1 T1:** Training session plan for patient navigators.

Day	Session	Time	Contents
Day 1	Registration	9:00 a.m.–9:15 a.m.	Registration of trainees and signature on attendance
	Opening session	9:15 a.m.–10:00 a.m.	Welcome of participants
			Introduction of facilitators and trainees
			Objectives and overview of training
			Ground rules and other logistics for the training
	Session 1: Your role as a CHW	10:00 a.m.–12:00 a.m.	
	1a. Interactive learning		Who are community health workers (patient navigators)?
			What are the roles and responsibilities of CHWs?
			What are topics to educate community women on cervical cancer?
			What are the specific services CHWs can provide to promote CCS?
	1b. Group activities		Small group work
	Session 2: Understanding the female genital organs	12:00 a.m.–1:00 p.m.	What are external female genital organs?
			What are internal female genital organs?
			How does a cervix look during a naked-eye examination?
	2a. Group activities		Small group work
	Lunch break	1:00 p.m.–2:00 p.m.	
	Summary of the day's activities	2:00 p.m.–2:30 p.m.	To be presented by trainees
	Discussion on the next day's agenda	2:30 p.m.–3:00 p.m.	To be led by facilitators
Day 2	Review of the previous day's activities and question-answering	9:00 a.m.–9:30 a.m.	Trainees present key points
			Discussion to be led by facilitators to answer any questions
	Session 3: Introduction to cervical cancer, causes, risk factors, and signs, and symptoms	9:30 a.m.–1:00 a.m.	
	3a. Interactive learning		What is cervical cancer?
			What causes cervical cancer?
			How does HPV cause cervical cancer?
			Who are at risk for cervical cancer?
			What are the signs and symptoms of cervical cancer?
	3b. Group activities		Small group work
	Lunch break	1:00 p.m.–2:00 p.m.	
	Session 4: Learning about the prevention of cervical cancer	2:00 p.m.–4:00 p.m.	
	4a. Interactive learning		What are the ways to prevent cervical cancer?
			Who should be screened for cervical cancer?
			What are the common cervical cancer screening tests?
			What is VIA?
			What preparation is necessary before a woman goes for a screening test?
			How frequently should a woman be screened for cervical cancer?
			Do women feel any discomfort during the screening tests?
	4b. Group activities		Roleplay
	Summary of the day's activities	4:30 p.m.–4:45 p.m.	
	Discussion on the next day's agenda	4:45 p.m.–5:00 p.m.	
Day 3	Review of the previous day's activities and question-answering	9:00 a.m.–9:30 a.m.	Trainees present key points and a discussion to be led by facilitators to answer any questions
	Session 5: Methods to improve women’s understanding of cervical cancer screening	9:30 a.m.–11:00 a.m.	
	5a. Interactive learning		How should CHWs deliver education intervention to women?
			What can you do to motivate women to be screened for cervical cancer?
	5b. Group activities		Roleplay
	Session 6: Making home visits	11:00 a.m.–1:00 p.m.	
	6a. Interactive learning		Why are home visits important?
			How should you to talk to a woman who misses her scheduled appointment for screening?
	6b. Group activities		Group discussion
	Lunch break	1:00 p.m.–2:00 p.m.	
	Session 7: Getting to know the screening service centers in your locality	2:00 p.m.–4:00 p.m.	
	7a. Interactive learning		What does a screening center for cervical cancer prevention mean?
			What are the delivery points for CCS services?
			What screening services are provided at the screening facilities?
	7b. Group activities		Roleplay
	Summary of the day's activities	4:00 p.m.–4:45 p.m.	To be presented by trainees
	Closing	4:45 p.m.–5:00 p.m.	

HPV, human papillomavirus; VIA, visual inspection with acetic acid.

### Implementation of patient navigation for community women

#### Study design, population, and setting

This will be a community-based randomized controlled trial to assess the effect of the patient navigation strategy on promoting cervical cancer screening, knowledge, health beliefs, and intention among community women. The study population is women living in a community in the Dar es Salaam region of Tanzania.

#### Sample size determination of COMW

The sample size for the COMW has been calculated through G-Power software (42) and is based on the outcome variable of completion of screening at a 6-month follow-up. Using the F-test, with an effect size of f = 0.3, α err prob = 0.05, and power (1 − β err prob) = 0.83, the sample size of community women to be recruited will be 202 (intervention group = 101 and control group = 101).

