### Outcome variables

The primary outcome of this study is the completion of CCS within 6 months in both the intervention group and control group (9–36, 39–41). Above 50% will indicate optimal screening uptake. The secondary outcome is the change in the level of knowledge, awareness, intention, and health beliefs toward cervical cancer and screening among the patient navigators and COMW after the training and education sessions (9, 47–50). For group items, >50% will indicate adequate knowledge, positive attitude, positive health beliefs, and being unaware of cervical cancer and CCS. Social demographic characteristics will be assessed to identify their association with the uptake of CCS services.

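### The stated sample size of 202 does not follow from f = 0.3 and power 0.83 in a two-arm trial: those inputs need 98 women, and 202 give about 99% power

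*Protocol article*

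**What the plan says.** Under 'Sample size determination of COMW', the protocol article says that the size was obtained in G-Power and "is based on the outcome variable of completion of screening at a 6-month follow-up". The inputs are given as "Using the F-test, with an effect size of f = 0.3, α err prob = 0.05", with power 0.83, and the result is that "the sample size of community women to be recruited will be 202", split 101 and 101. The section does not give the type of F-test, the numerator degrees of freedom, an allowance for loss, or an expected screening proportion in either arm.

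The 'Randomization' section confirms two arms at 1:1. The 'Outcome variables' section confirms what is being compared: "The primary outcome of this study is the completion of CCS within 6 months in both the intervention group and control group". That is a yes/no outcome. The only background figure for uptake is in 'Cervical cancer in Tanzania', where "only 6%–21% of women participate in CCS".

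**The concern.** Effect size, alpha, power and sample size are all printed. For a comparison of two groups, any three of them fix the fourth. An f of 0.3 is a fairly large effect, and 202 women look like too many for 83% power.

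If the figures conflict, a reader cannot tell whether the trial was sized for f = 0.3 with much higher power than stated, or for a smaller effect with 83% power. Because f is not translated into uptake, the reader also cannot recover the difference in screening completion that the trial was designed to detect. This paragraph is the only justification given for the sample size of the primary comparison.

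**Working it through.** **Inputs.** f = 0.3, alpha = 0.05, power = 0.83 and N = 202 (101 + 101) come from 'Sample size determination of COMW'. Two arms at 1:1 come from 'Randomization'. Four assessment times (T0 to T3) come from 'Data collection and measures'.

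**Formula.** For a fixed-effects F-test with g groups, the noncentrality parameter is λ = N·f². Power is the probability that a noncentral F(df1, N − g, λ) exceeds the 95th percentile of the central F(df1, N − g). For two arms, df1 = 1 and g = 2.

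**Attempt to reproduce 202 as a two-arm comparison.**

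| N | λ = 0.09·N | Critical F(1, N − 2) | Power |
|---|---|---|---|
| 96 | 8.64 | 3.942 | 0.829 |
| 97 | 8.73 | 3.941 | 0.833 |
| 98 | 8.82 | 3.940 | 0.836 |
| 202 | 18.18 | 3.888 | 0.989 |

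The smallest N reaching 0.83 is 97, or 98 with equal arms. The stated 202 is about twice that (202/98 = 2.06). Solving instead for f with N = 202 and power 0.83 gives f = 0.206.

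**Could loss to follow-up explain it?** No allowance is stated. Going from 98 to 202 would need a loss of 1 − 98/202 = 51.5%.

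**Could a different F-test explain it?** With f = 0.3 and power 0.83:
- One-way ANOVA with 3, 4 or 8 groups needs 120, 136 or 184.
- Repeated-measures tests with two to four measurements, under the default effect-size convention, need at most 97.
- With df1 from 1 to 15, only df1 = 10 gives 202: power is 0.831 to 0.832 at N = 202, and just under 0.83 at N = 201. df1 = 9 gives 194 to 195, and df1 = 11 gives 209 to 210.

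Two arms at four times yield effects with 1 or 3 df, or 7 df across all eight cells. None has 10.

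**What the figures mean on the yes/no scale.** For two equal groups with proportions p₁ and p₂, f = [(p₂ − p₁)/2] / √{[p₁(1 − p₁) + p₂(1 − p₂)]/2}.
- 6% v 27.4%: 0.107/√0.1277 = 0.107/0.357 = 0.30.
- 21% v 48.4%: 0.137/√0.2078 = 0.137/0.456 = 0.30.

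The usual two-proportion power, with p̄ = (p₁ + p₂)/2, is Φ{[(p₂ − p₁)√n − 1.96·√(2p̄(1 − p̄))] / √[p₁(1 − p₁) + p₂(1 − p₂)]}. With n = 101 per arm it is 98.7% for either pair, and 51 per arm would suffice for 83%. The conflict is therefore the same on the binary scale.

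**What 101 per arm detects with 83% power.** Solving the same formula for p₂ gives 6% v 19.6%, 13.5% v 30.3% and 21% v 39.7%. To check the last pair: p̄ = 0.3035; (0.187 × 10.05 − 1.96 × 0.650)/0.637 = (1.879 − 1.274)/0.637 = 0.95; Φ(0.95) = 0.83. These figures make no allowance for clustering by navigator or for loss.

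**The case against.** The article does not name the type of F-test, and a condensed article may leave the software settings to the full protocol. Several settings do reach 202: an overall regression F-test with 10 predictors (linear regression is among the planned analyses), or a four-measurement repeated-measures test under another effect-size convention with sphericity near 0.54. A slip that read the total of 98 as a per-arm number would give 196, which is close. So a reader might infer that 202 can arise only from 10 numerator degrees of freedom, or from a mistaken entry of 11 groups. The documents do not support that; the cause is unknown. What stands is that none of these settings is stated, and the 10-df test would not be the comparison of the two arms.

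A reader might also infer that an F-test effect size has no meaning for a yes/no outcome. That goes too far. A 1-df F-test on 0/1 data is close to a two-proportion test, and f = 0.3 translates into the proportions shown above. The mismatch of scale does not produce the factor of two. The fair criticism is narrower: the proportions behind f = 0.3 are not given.

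Finally, it is tempting to conclude that the trial is underpowered or that a null result could not be interpreted. Neither follows. The error is towards more women than the inputs need, and a null result can still be read from its estimate and confidence interval.

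**Conclusion.** The printed figures conflict for the two-arm 1:1 design. With f = 0.3, alpha 0.05 and power 0.83 the comparison needs 97 to 98 women, not 202. With 202 women the power is 98.9%, not 83%, or the detectable f is 0.206, not 0.3. This rests on reading the F-test as the comparison of the two arms, which is what the stated primary outcome requires, with independent observations and no loss.

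The effect size is also not linked to any uptake proportions, so the difference in screening completion that the trial was sized for is unclear. The number of women is not too small for the effect stated; the justification for it is not reproducible. The paragraph is wrong as written and should be corrected, but the point does not threaten the trial's validity.

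**What to change.** Keep 202 and replace the F-test sentence with a two-proportion statement: 101 women per arm, two-sided alpha 0.05, the assumed control proportion, and the completion proportion detectable with the stated power. The control proportion should be labelled as an assumption and a range shown. For illustration, 101 per arm gives 83% power for about 6% v 20%, 13.5% v 30% or 21% v 40%, before any allowance for clustering and loss.

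The 6% to 21% in the background section should not be presented as the control rate. It describes participation in screening generally, whereas the trial enrols women never screened before and counts completion within six months. The documents do not give that rate. The second member of each illustrative pair is solved back from 202 and 0.83, so the investigators should also say whether such a difference is the one they wanted to detect.

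Alternatively, if f = 0.3 is kept as the design effect, state the F-test as a two-group comparison, correct the power to about 99%, and give the proportions that f = 0.3 represents.

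Either way the cost is rewording one paragraph, with no change to recruitment.

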#### Recruitment of the COMW

After the 3-day training, the patient navigators and researchers will conduct one-to-one home visits to select participants from the Kinondoni ward in Dar es Salaam. Through a systematic sampling technique, the nth house will be selected and only one eligible woman will be recruited per household. Simple random sampling will be applied whenever more eligible women are found in one house to select only one participant. The inclusion criteria will be COMW aged 21–50 (18–23, 25, 27–29), no previous history of cancer (20, 23, 25, 27, 28), no previous CCS tests (22), able to speak native Swahili language (19, 21, 23), no plan to move residence during the 6-month study period (19, 23, 27), non-pregnant (22), and willing to participate in the study (21–23). They will be excluded from the study only if they are unable to comprehend the information provided due to mental illness and if they have mobility difficulties, and those who are absent at the time of collecting baseline data will also be excluded. The patient navigators will provide details about the study and will ask the COMW to complete the consent process. The researchers will administer questionnaires to obtain baseline data for all the eligible COMW willing to participate in the study (21–23).

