### Randomization

The study participants will be randomized 1:1 into the intervention group (*n* = 101) and control group (*n* = 101). A random sequence will be generated in an Excel spreadsheet, followed by the use of the Excel RAND function-random number-sort. The COMW in the intervention group will be notified of the date and place of the intervention.

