### Intervention group

The participants randomly assigned to the intervention group will receive health education, help to schedule screening appointments, navigation services, counseling, and follow-up care from the patient navigators. Regarding health education, each patient navigator will deliver a one-time group education session for 13 COMW (19–23, 28) that will last for 6 h (21, 28). The education session will be interactive and conducted using a PowerPoint, projector, and flipchart to help the COMW understand the content clearly (18–23, 25, 29). During the education session, free drinks will be given to the COMW to make them feel comfortable. The education session will have 4 sessions within the 6 h, whereby session 1, scheduled for 1 h, will be an opening session that allows everyone to introduce themselves and the objective and logistics to be communicated. Session 2 is scheduled for 1 h to cover female reproductive organs and session 3, scheduled for 2 h, is an introduction to cervical cancer, including the cause, risk factors, signs, and symptoms of cervical cancer. Session 4 is scheduled for 2 h to cover the preventive measures for cervical cancer. Please refer to Table 2 for further details. After delivering this one-time health education to the COMW, the patient navigators will begin to provide navigation services during follow-ups, such as scheduling screening appointments, escorting the women to the screening center, taking care of the mother's child, encouraging participants to attend the screening centers for their appointments, and counseling to those who fail to attend the screening center for their appointment.

**Table 2 T2:** Session plan for delivering health education to community women.

Session	Time	Contents
Opening session	12:00–13:00	Welcome of participants
		Introduction of facilitators and learners
		Objectives and overview of health education
		Ground rules and other logistics during health education
Session 2: Understanding the female genital organs	13:00–14:00	What are external female genital organs?
		What are internal female genital organs?
		How does a cervix look during a naked-eye examination?
Discussion		
Session 3: Introduction to cervical cancer, including its causes, risk factors, signs, and symptoms	14:00–16:00	What is cervical cancer?
		What causes cervical cancer?
		What are the risks for cervical cancer?
		What are the signs and symptoms of cervical cancer?
Discussion		

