The outcome of patient navigation is hypothetically assumed to be positive, with increases in screening uptake and knowledge, positive health beliefs, and intention. This should be associated with the proximity of the patient navigators and the COMW. Since they live in the same area, know each other, and share most of the cultural elements, they are likely to listen to each other and cooperate on whatever is agreed. When patient navigators deliver health education, it is likely to be well received and understood because it is delivered in a non-formal structure. Furthermore, when the patient navigators ask the COMW to screen for cervical cancer, they are likely to do so because the patient navigators could conduct a follow-up at any time at their homes. Therefore, COMW may screen not because of health education, but because they know the patient navigators will conduct a follow-up. Meanwhile, when women are asked to become patient navigators, they accept because they know it will benefit them financially. Since they consider this work as employment, an allowance inevitably amplifies their commitment to learning and implementing. Therefore, based on the definition that patient navigators can be volunteer or be paid, in the Tanzanian context, paying patient navigators is good, as volunteering could be associated with the poor implementation of patient navigation. This is consistent with a previous study that reported that patient navigators’ incentives and remuneration are core issues that affect the performance of individual patient navigators and the overall performance of the CHW program. This previous study recommends that patient navigators receive a financial package that corresponds to their job demands, complexity, number of hours worked, training, and the roles they undertake (54).

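### Trained navigators explain the study to, and seek consent from, women who later become controls: an avoidable partial exposure of unknown size

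*Protocol article*

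**What the plan says.** The section Recruitment of the COMW opens with this statement: "After the 3-day training, the patient navigators and researchers will conduct one-to-one home visits to select participants from the Kinondoni ward in Dar es Salaam". In the same section, "The patient navigators will provide details about the study and will ask the COMW to complete the consent process", while "The researchers will administer questionnaires to obtain baseline data for all the eligible COMW willing to participate in the study". Navigators and researchers are therefore on the same visits, and the explanation and consent request are assigned to the navigators.

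The training comes first. For session 5 the text says that "the patient navigators will learn how to deliver health education and encourage women to complete screening"; session 6 covers home visits (Training patient navigators, and Table 1).

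Under Randomization: "The study participants will be randomized 1:1 into the intervention group" or the control group, 101 women in each. Under Intervention group, the intervention women receive education, help with appointments, navigation services, "counseling, and follow-up care from the patient navigators". Under Control group, the other women have usual care only: the national campaign, media, friends and relatives. Navigator contact is not part of that condition.

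The Discussion, writing of navigators and community women, says "Since they live in the same area, know each other, and share most of the cultural elements", and expects the women to listen and cooperate for that reason. It adds that women may go for screening because they expect a navigator to follow them up, rather than because of the education.

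**The concern.** The people who deliver the intervention also make the recruitment approach to both future arms, after being taught how to encourage screening. Women enrolled have had no previous screening test, so a home conversation about a screening study with a trained local woman may itself be a prompt. Some controls may also expect her to return, which the Discussion offers as a reason why women may attend.

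If part of the intervention's effect reaches controls this way, uptake in the control arm rises and the estimated benefit on the primary outcome, completion of screening within 6 months, is biased towards zero. With no record of navigator contact by arm, a small observed effect would be harder to interpret. The exposure follows from a stated allocation of tasks, and the same section shows that another team is present to do the task.

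**Working it through.** **Does the exposure follow from the text?**

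1. Navigators are trained before recruitment (Recruitment of the COMW; Table 1, sessions 5 and 6).
2. Navigators explain the study and ask for consent, for every woman recruited (Recruitment of the COMW).
3. The recruited women are then randomised individually, 101 v 101 (Randomization). Half of the women approached and enrolled in this way are therefore controls.
4. The same navigators deliver the intervention (Intervention group), and controls are meant to have usual care without them (Control group).
5. Researchers are on the same visits and administer the baseline questionnaire to every consenting woman (Recruitment of the COMW).

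Steps 1 to 4 establish contact with controls. Step 5 shows that navigators need not be the ones to explain the study and take consent.

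**The plan's own figure.** Sample size determination gives 202 women for an F-test with f = 0.3, alpha 0.05 and power 0.83. As a plain two-arm test (numerator df 1, noncentrality f² × N), N = 97 reaches 0.83, and N = 202 gives 0.09 × 202 = 18.18 and power 0.989. So 202 is not reproduced as a two-arm test. That is a separate matter; only the 101 per arm is used below.

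**Illustration of dilution.** The document gives no exposure share, so it is varied.

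- p0 = 21%, the top of the 6%–21% screening participation quoted for Tanzania.
- p1 = 56%, the low end of the 56%–89% quoted for navigator studies, read here as uptake; or p1 = 41%, an assumption chosen to show a smaller effect.
- c = share of controls who gain the full intervention effect (assumed).
- Diluted control rate: p0' = p0 + c(p1 − p0). Difference: (1 − c)(p1 − p0).
- Power, two-sided 0.05, n = 101 per arm: Φ{(d − 1.96·s0)/s1}, where d = p1 − p0', s0 = √[2p̄(1 − p̄)/n], s1 = √{[p0'(1 − p0') + p1(1 − p1)]/n} and p̄ is the mean of the two rates.

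For 56% v 21% with c = 0.2: p0' = 0.21 + 0.2 × 0.35 = 0.28; d = 0.28; p̄ = 0.42; s0 = 0.0695; s1 = 0.0666; (0.28 − 0.136)/0.0666 = 2.16; power 0.985.

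For 41% v 21% with c = 0.2: p0' = 0.25; d = 0.16; p̄ = 0.33; s0 = 0.0662; s1 = 0.0652; (0.16 − 0.130)/0.0652 = 0.465; power 0.679.

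| c | 56% v 21%: difference (points) | power | 41% v 21%: difference (points) | power |
|---|---|---|---|---|
| 0 | 35.0 | 1.00 | 20 | 0.873 |
| 0.1 | 31.5 | 0.997 | 18 | 0.787 |
| 0.2 | 28.0 | 0.985 | 16 | 0.679 |
| 0.3 | 24.5 | 0.945 | 14 | 0.556 |

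The estimate shrinks by the share c in every case. Whether power suffers depends on how large the true effect is.

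**The case against.** The strongest reply is that the recruitment visit is not the intervention. The Intervention group section places navigation services after the group education session, and at recruitment the navigators are asked only to describe the study and seek consent. Nothing says that they encourage screening there. This stands: the exposure is partial, and a reader who infers that controls receive the intervention goes beyond the text.

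Second, the visit precedes randomisation and is common to both arms, so the randomised comparison remains valid. This also stands. Dilution arises only so far as the visit does for controls part of what the later navigation does for intervention women. If it raised uptake equally in both arms, the difference would not shrink.

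Third, the Discussion passage is speculative. It says that closeness helps education and requests to be well received, and that expected follow-up may drive attendance; follow-up is offered only to the intervention arm. It does not single out contact as what makes the intervention work, and it describes navigators and women, not all the women in the ward, as knowing each other. It does support the weaker statement that navigator contact is not neutral.

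Fourth, the 10% to 30% shares give some controls the full effect of a 6-hour session plus escorting and counselling, which is a lot to attribute to a consent conversation. Agreed; they are illustrations.

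Fifth, scripts, contact rules and questionnaire items may be in the full protocol. The point therefore does not rest on their absence but on the task that the article does assign.

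Sixth, the researchers' baseline questionnaire may also prompt controls, and spread within the ward would continue. Both are true; the change removes only the avoidable part.

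**Conclusion.** The point holds as a cheap improvement to a stated design choice. Trained navigators approach, inform and seek consent from women who will be controls, although researchers on the same visit could do so. The likely direction is a smaller between-arm difference; its size cannot be computed from the document.

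A reader might infer from the 41% v 21% column that the trial is underpowered. The documents do not support that: the 41% and every exposure share are assumptions, and with 56% v 21%, taken from the Introduction's figures, power stays at 0.945 or above up to a 30% share. What is supported is an avoidable dilution of unknown size, not a demonstrated loss of power and not an invalid comparison.

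**What to change.** In Recruitment of the COMW, have the researchers explain the study from a neutral script and take consent, with navigators at most introducing them at the door. State that, after allocation, navigators make no screening-related contact with controls before T3.

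Add a short question for all women on whether a navigator has been in contact with them about screening. Preferably ask it at T3 only, so that asking does not itself prompt screening during follow-up. Report the answers by arm and keep the primary analysis as randomised. The question describes exposure; it cannot by itself separate a true null from contamination.

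The cost is a change of wording and one item in a household visit that is already planned, with no extra staff and no cluster design. The downside is less use of the navigators' local trust at consent, so recruitment may be slightly slower. Some spread within the ward will remain.
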